## Research information

|                  |                                                                                                                                                                                                                                                                                                                                                                                                                                                                                                                                                                                                                                                                                                                                                                 |
|------------------|-----------------------------------------------------------------------------------------------------------------------------------------------------------------------------------------------------------------------------------------------------------------------------------------------------------------------------------------------------------------------------------------------------------------------------------------------------------------------------------------------------------------------------------------------------------------------------------------------------------------------------------------------------------------------------------------------------------------------------------------------------------------|
| Rationale | It is known that inadequate quantity and quality of sleep is negatively associated with health and wellbeing of the sick and the healthy (1-4). In patients, the lack of sleep is associated with physiological disturbances such as respiratory and metabolic changes, which may result in poor healing (5-10). In a recently performed single-day, multicentre, observational study coordinated by section acute medicine of VUmc, 2005 patients in 39 hospitals were asked about the sleep quality and quantity of the previous night and their habitual sleep at home a month before admission. This study, recently published in JAMA internal medicine, found that both the quality and quantity of sleep of in-patients were negatively affected, due to |
|------------------|-----------------------------------------------------------------------------------------------------------------------------------------------------------------------------------------------------------------------------------------------------------------------------------------------------------------------------------------------------------------------------------------------------------------------------------------------------------------------------------------------------------------------------------------------------------------------------------------------------------------------------------------------------------------------------------------------------------------------------------------------------------------|

|                   |                                                                                                                                                                                                                                                                                                                                                                                                                                                                                                                                                                                                                                                                                                                                                                                                                                                                                                                                                                                                                                                                                                                                                                                         |
|-------------------|-----------------------------------------------------------------------------------------------------------------------------------------------------------------------------------------------------------------------------------------------------------------------------------------------------------------------------------------------------------------------------------------------------------------------------------------------------------------------------------------------------------------------------------------------------------------------------------------------------------------------------------------------------------------------------------------------------------------------------------------------------------------------------------------------------------------------------------------------------------------------------------------------------------------------------------------------------------------------------------------------------------------------------------------------------------------------------------------------------------------------------------------------------------------------------------------|
|                   | 
many hospital-related factors such as noise of other patients, noise of hospital equipment, pain and toilet visits (11).
 
A few studies on the effectiveness of interventions to improve the quality of sleep have been conducted in the past, mainly on the Intensive Care (IC) Unit. Interventions such as providing patients with earplugs and sleeping masks, dimming the hallway lights, involving patients in what they need to improve their sleep and implementing sleep hygiene education for nurses have been found to improve both sleep quantity and quality in the IC units (12-15). However, no large scale multicentre studies have been performed on the potential effectiveness of these interventions in regular wards. Therefore, the aim of this study is to implement interventions (such as care-clustering, better mattresses/pillows/blankets, the distribution of earplugs and sleep masks, sleep education to patients, nurses and doctors, adjustment of the hospital rhythm (15)) and to measure whether these interventions have a positive effect on the (experienced and absolute) quality and quantity of sleep in regular hospital wards.
 |
| Aim        | 
Primary outcome measure:
 
 
- The effect of implemented sleep interventions on the quantity of sleep.
 
 
Secondary outcome measures:
 
 
- To explore the potential effects of the interventions on other sleep outcomes, the use of sleep medication, length of stay (including discharge diagnosis: homewards/palliative policy/rehabilitation etc), incidence of delirium and incidence of ICU admissions from the clinical wards.
 
                                                                                                                                                                                                                                                                                                                                                                                                                                                                                                                                                                                                                                           |
| Design     | 
Before and after study.
 
 
- 8 months baseline measurement
 
- 3 months preparation of interventions
 
- 8 months introduction of intervention and measurement
 
                                                                                                                                                                                                                                                                                                                                                                                                                                                                                                                                                                                                                                                                                                                                                                                                                                                                                                                                                      |
| Population | 
All <math>\geq 18</math>-year-old medical patients admitted for at least one night to one of the participating wards.
                                                                                                                                                                                                                                                                                                                                                                                                                                                                                                                                                                                                                                                                                                                                                                                                                                                                                                                                                                                                                                                            |

|                           |                                                                                                                                                                                                                                                                                                                                                                                                                                                                                                                                                                                                                                                                                                                                                                                                                                 |
|---------------------------|---------------------------------------------------------------------------------------------------------------------------------------------------------------------------------------------------------------------------------------------------------------------------------------------------------------------------------------------------------------------------------------------------------------------------------------------------------------------------------------------------------------------------------------------------------------------------------------------------------------------------------------------------------------------------------------------------------------------------------------------------------------------------------------------------------------------------------|
| Inclusion criteria | 
 
- <math>\geq 18</math> years of age
 
- Admitted to Acute Medical Units (AOA), internal medicine/nephrology wards or vascular diseases/urology unit (with the possibility to extend the research to other wards)
 
- Able to give informed consent
 
- Admission to the ward admitted before 3:00 AM that day
 
                                                                                                                                                                                                                                                                                                                                                                                                                                            |
| Exclusion criteria | 
 
- <math>< 18</math> years of age
 
- Not able to give informed consent (i.e. severe illness, not capable of speaking Dutch, cognitive dysfunction)
 
- Admission to the ward after 3:00 AM that day
 
                                                                                                                                                                                                                                                                                                                                                                                                                                                                                                                                                          |
| Sample size        | 
Similar research has, by our knowing, has only been done at the ICU. Patients at the ICU will have different reasons for sleep disruption and therefore we cannot use these data to calculate a sample size. Based on our previous research, we aim to include 286 patients in each group.
                                                                                                                                                                                                                                                                                                                                                                                                                                                                                                                               |
| Recruitment        | 
Every workday a researcher will identify together with the treating doctor or intern all potential eligible patients. They will be asked to participate in this project. When patients agree to participate and sign the informed consent document, the patient will receive a sleep registration bracelet for two nights. The following two mornings one of the researchers will visit the patient before 12:00 A.M. for a short interview. The questionnaires will contain questions concerning sleep quality and quantity of the prior night and a month before admission. All data will be registered in the protected Castor database. The results of the sleep registration bracelets will be coded with the record number generated by Castor. The bracelets will be re-used after sterilisation in the hospital.
 |
| Intervention       | 
Interventions:
 
Interventions will be developed in close consultation with clinicians and patients after the baseline data has been collected.
 
Interventions could focus on:
 
 
- Better (comfortable) mattresses/pillows/blankets
 
- Earplugs, sleep masks
 
- Door stops, light strips in hall way, dimmable lights
 
                                                                                                                                                                                                                                                                                                                                                                                                                  |

|                               |                                                                                                                                                                                                                                                                                                                                                                                                                                                                                                                                                                                                                                                                                                                                                                                                                                                                                                                                                                                                 |
|-------------------------------|-------------------------------------------------------------------------------------------------------------------------------------------------------------------------------------------------------------------------------------------------------------------------------------------------------------------------------------------------------------------------------------------------------------------------------------------------------------------------------------------------------------------------------------------------------------------------------------------------------------------------------------------------------------------------------------------------------------------------------------------------------------------------------------------------------------------------------------------------------------------------------------------------------------------------------------------------------------------------------------------------|
|                               | 
 
- Posters to increase awareness with medical team
 
- Sleep education patients (information flyer, inform about possibility to bring own pillow from home, etcetera)
 
- Sleep hygiene training nurses and doctors (awareness, “soft” shoes, use little light, if possible place restless patients in single room, during day time: stimulate patients to leave their beds, open curtains and blinds, discourage afternoon naps and caffeine after 15:00 PM, avoid giving I.V. drips overnight if possible or diuretics in the afternoon if not necessary with the aim of reducing nightly toilet visits, take only vitals when necessary)
 
- Adjust hospital rhythm (only measure vital signs in morning if indicated, wash patients after morning rounds)
 
- Exploring the possibility to use venflon cannulas instead of drips to increase freedom in movement.
 
- ward-specific plan of improvement
 
 |
| Study endpoints        | 
Measurements after first to fifth night:
 
 
- Short questionnaire (see Appendix F1, F2) 
 
o Sleep quality (Patient-Reported Outcomes Measurement Information System (PROMIS™) - based questions (11, 16))
 
o Sleep quantity (Consensus Sleep Diary (CSD)) (11, 17)
 
 
 
- Measured sleep quantity (with sleep tracker (e.g. Actigraph or FitBit))
 
 
After 30 days (from medical record):
 
 
- Length of stay (including discharge diagnosis: homewards/palliative policy/rehabilitation etc)
 
- Incidence of delirium
 
- Incidence of unplanned ICU admissions
 
                                                                                                                                                                                                                             |
| Other study parameters | Age, sex, number of patients in room, use of sleep medication and other sleep promoting interventions, potential sleep disturbing                                                                                                                                                                                                                                                                                                                                                                                                                                                                                                                                                                                                                                                                                                                                                                                                                                                               |

|                                                |                                                                                                                                                                                                                                                                                                                                                                                                                                                                                                                                                                                                                                                                                                                                                                              |
|------------------------------------------------|------------------------------------------------------------------------------------------------------------------------------------------------------------------------------------------------------------------------------------------------------------------------------------------------------------------------------------------------------------------------------------------------------------------------------------------------------------------------------------------------------------------------------------------------------------------------------------------------------------------------------------------------------------------------------------------------------------------------------------------------------------------------------|
|                                                | factors (i.e. use of diuretics, drips), MEWS scores, Clinical Frailty index, Charlson Comorbidity Index , clinical diagnosis)                                                                                                                                                                                                                                                                                                                                                                                                                                                                                                                                                                                                                                                |
| Statistical analyses                    | 
Analysis will mainly focus on the first night collected data.
 
Descriptive data-analyses will provide mean, median, 95% confidence intervals (CI) and inter-quartile ranges (IQR) for continuous variables and percentages for categorical variables.
 
Mean difference scores in sleep quantity (Actigraphy) and quality (PROMIS total score) will be compared between groups (intervention- and control group). Confounding and effect modification were assessed using multiple linear regression analysis.
 
Normality will be checked by visual inspection of histograms.
 
p-values of <0.05 will be considered statistically significant. Analysis will be performed using Statistical Package for Social Sciences for Windows (SPSS).
 |
| Burden for patients                     | 
Sleeping with a wrist band
 
Filling out questionnaires up to five times (time investment 10 minutes)
                                                                                                                                                                                                                                                                                                                                                                                                                                                                                                                                                                                                                                                            |
| Potential risk for patients             | No risks applicable                                                                                                                                                                                                                                                                                                                                                                                                                                                                                                                                                                                                                                                                                                                                                          |
| Advantages of participating in study    | At this moment there are no advantages for the patient to participating in this study. In the future we hope to increase awareness and on the basis of the results of the interventions improve the quality and quantity of sleep in hospitalized patients in the Netherlands.                                                                                                                                                                                                                                                                                                                                                                                                                                                                                               |
| Disadvantages of participating in study | It takes a few minutes to fill out the questionnaire                                                                                                                                                                                                                                                                                                                                                                                                                                                                                                                                                                                                                                                                                                                         |
| Patient reimbursement                   | No compensation applicable                                                                                                                                                                                                                                                                                                                                                                                                                                                                                                                                                                                                                                                                                                                                                   |
| Administrative aspects                  | No traceable patient data will be collected. Data will be saved in a secured Castor database. Data will be analysed in the Amsterdam UMC, Location VUmc.                                                                                                                                                                                                                                                                                                                                                                                                                                                                                                                                                                                                                     |

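### Wards may be added with no requirement that they be measured in both periods, so a change in ward mix can be counted as intervention effect

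*Protocol*

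**What the plan says.** All references are to the rows of the table under Research information in the protocol.

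- **Design:** "Before and after study", with 8 months of baseline, 3 months of preparation and 8 months of intervention. No concurrent control is described, so the control group is taken to be the baseline patients.
- **Population:** "medical patients admitted for at least one night to one of the participating wards". Nothing says that the same wards take part in both periods.
- **Inclusion criteria:** acute medical, internal medicine/nephrology and vascular/urology units, "with the possibility to extend the research to other wards". No date, trigger or baseline condition is attached to the extension.
- **Sample size:** "we aim to include 286 patients in each group", with no target by ward.
- **Statistical analyses:** mean sleep quantity and quality "will be compared between groups (intervention- and control group"). The next sentence reads "Confounding and effect modification were assessed using multiple linear regression analysis". It names no covariates.
- **Other study parameters:** the list begins "Age, sex, number of patients in room, use of sleep medication and other sleep promoting interventions, potential sleep disturbing" and goes on to illness severity, frailty, comorbidity and diagnosis. Ward does not appear in it.
- **Intervention:** one possible component is a "ward-specific plan of improvement".

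**The concern.** In an uncontrolled before-after study the inference rests on the two periods being comparable. Wards can differ in mean sleep for reasons unrelated to the intervention, such as noise, routine, layout and case mix. If a ward contributes patients to the intervention period only, its difference from the other wards enters the intervention mean and has no counterpart in the baseline mean. A quieter ward would make the intervention look better, and a noisier one could hide a real benefit.

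The both-periods condition belongs in the protocol. Once the baseline period has closed, no analysis plan can create the missing baseline patients. The protocol leaves the condition open in the same row where it allows wards to be added.

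**Working it through.** **The plan's own figure.** The 286 per group cannot be reproduced, because no effect size, SD, power or dropout is stated. Unrelated assumptions come close: 30 min with SD 120 at 85% power gives 288, and 25 min with SD 90 at 90% power and 5% dropout also gives 288. The figure is neither confirmed nor refuted, so it is used here only to find what difference it can detect.

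**Detectable difference.** With the protocol's 5% level, assumed two-sided:

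- sqrt(2/286) = 0.0836
- 80% power: 0.0836 × (1.960 + 0.842) = 0.234 SD
- 90% power: 0.0836 × (1.960 + 1.282) = 0.271 SD
- For an assumed SD of 60 to 120 min, 0.234 SD is about 14 to 28 min.

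**Bias of the unadjusted comparison.** Let *p* be the share of intervention patients from a ward with no baseline patients, and *w* that ward's difference in mean sleep from the other wards, in SD units. With a true effect of zero:

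- bias = *p* × *w*
- standard error = sqrt[(1 + 1 + *p*(1 − *p*)*w*²)/286]
- type I error = P(Z > 1.96 − bias/SE) + P(Z < −1.96 − bias/SE)

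Both *p* and *w* are assumptions, since the protocol gives neither.

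| *p* | *w* (SD) | Bias (SD) | Bias / 0.234 | Two-sided type I error |
|---|---|---|---|---|
| 0.10 | 0.2 | 0.02 | 9% | 5.7% |
| 0.10 | 0.5 | 0.05 | 21% | 9.1% |
| 0.20 | 0.2 | 0.04 | 17% | 7.7% |
| 0.20 | 0.3 | 0.06 | 26% | 11% |
| 0.20 | 0.5 | 0.10 | 43% | 22% |
| 0.30 | 0.3 | 0.09 | 38% | 19% |
| 0.30 | 0.5 | 0.15 | 64% | 43% |

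Worked line for *p* = 0.20, *w* = 0.3: bias = 0.06; SE = sqrt(2.0144/286) = 0.0839; bias/SE = 0.715. Type I error = P(Z > 1.245) + P(Z < −2.675) = 0.107 + 0.004 = 0.11.

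In minutes, a ward differing by 30 min and supplying 25% of intervention patients gives 0.25 × 30 = 7.5 min. One differing by 45 min and supplying 33% gives 0.33 × 45 = 14.9 min.

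**What regression can do.** Two cases arise for a ward seen only in the intervention period:

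1. Ward is not in the model. The bias stays, less whatever the recorded patient covariates absorb.
2. Ward is in the model. That ward's own term takes up its mean, so its patients add essentially nothing to the period contrast.

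If every ward contributes to both periods and ward is a model term, the ward-mix bias is removed, assuming a common effect across wards.

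**The case against.** The protocol does provide for confounding to be assessed by multiple linear regression, and ward could be one of the covariates. The covariate list commonly belongs in a statistical analysis plan, which is not shown, so its absence here is not a fault. The recorded variables (patients per room, severity score, frailty, comorbidity, diagnosis, disturbing factors) overlap with much of what makes wards differ. All of this stands, and it limits the bias figures to the unadjusted comparison.

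A reader might go further than the text allows in four ways:

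- **That wards will be added while the study runs.** The protocol gives no timing. The extension could equally take place before or during baseline. Interventions are to be designed after baseline data are in and may be tailored by ward, which fits wards that have their own baseline, though it does not require it.
- **That ward is excluded from the analysis because it is not among the other study parameters.** That row lists data to be collected, not model terms, and ward is known for every patient through eligibility.
- **That keeping the same wards is the design's only protection.** The planned regression is another.
- **That the three named units will shift in share even with no new ward.** This is possible, but researchers are to approach all potentially eligible patients each workday, and nothing in the protocol points to a material shift.

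The gap in the eligibility rule remains. Regression cannot supply a within-ward contrast for a ward that has patients in only one period.

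**Conclusion.** The point holds in a limited form. The ward set is open, no rule ties an added ward to both periods, and the stated comparison is of the two groups as a whole. A change in ward mix can therefore be counted as intervention effect. It would be wrong to say that it will be: this depends on whether and when wards are added, and on whether ward enters the regression.

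The size cannot be fixed from the protocol. On assumed shares and ward differences it runs from negligible (10% share, 0.2 SD) to 0.06-0.15 SD, or 26% to 64% of the difference detectable at 80% power (20-30% share, 0.3-0.5 SD). The direction is unknown. This is an inexpensive improvement to the plan and does not by itself invalidate the design.

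**What to change.** 1. In the Inclusion criteria row, state that a ward enters the primary comparison only if it has patients measured in both the baseline and the intervention period.
2. In the Statistical analyses row, state that the regression giving the primary estimate includes ward as a fixed effect.
3. Report wards without baseline data descriptively.

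The text cost is a few sentences, and no new data are needed. The downside is that patients from wards without baseline data leave the primary analysis. If they made up 20% or 30% of the 286 intervention patients, about 229 or 200 would remain. The detectable difference at 80% power would rise from 0.234 SD to about 2.80 × sqrt(1/286 + 1/229) = 0.248 SD, or 2.80 × sqrt(1/286 + 1/200) = 0.258 SD. Counting the recruitment target over wards measured in both periods would avoid this loss. The change deals with ward mix only, not with other differences between the two periods.
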